**Methods:**

The study will be a prospective, cluster randomized controlled trial involving 440 patients with AF in 8 community health service centers (clusters) in Shanghai, China. The SDM group will receive anticoagulation management through the novel SDM tool, while the control group will receive standard care. The follow-up period will be at least 2 years. The primary outcome will be any bleeding event, while secondary outcomes include the accordance of stroke prophylaxis for AF according to the current guidelines, time in therapeutic range (TTR), the occurrences of major bleeding and thrombosis events, and patient knowledge, adherence, and satisfaction.

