
## Methods

### Study design

This study will be a cluster randomized controlled trial conducted from October 2022 to April 2024 in eight community health service centers in Shanghai, China. The trial will compare the efficacy of using the shared decision-making (SDM) tool, I-Anticoagulation, versus the usual care in treating patients with AF. The clusters will be randomly assigned to either the SDM or control group, as depicted in Fig. 1. Consecutive patients with AF will be enrolled in the study, with those in the SDM group being treated using the I-Anticoagulation tool, while those in the control group receiving standard care. The study was registered on July 23, 2022, in the Chinese Clinical Trial Registry, with the registration number ChiCTR2200062123. This protocol was designed and described according to the standard protocol item—Recommendations for Interventional Trials–Artificial Intelligence (SPIRIT-AI) extension published in 2019 [25] (see Additional file 1).

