### Randomization and blinding

To avoid any risk of contamination between the SDM and control groups, cluster randomization will be implemented in this trial. The intervention provided to patients with AF will be grouped by clinicians in a single community health service center. Computer-generated randomization will be used to allocate the intervention and control groups in a 1:1 ratio following AF confirmation. The allocation results of each community health center will be told to the administrators by telephone. Each administrator only knows the result of his or her own site. The researchers, participants, and data analysts will not be blinded, but the participants will not be allowed to know the outcomes of this study.

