### Interventions

#### Introduction

Community health service centers that are randomized to the SDM group will utilize the SDM tool to manage AF patients. The medical specialists involved in this study will have access to the SDM tool. The anticoagulation regimens for AF patients will be determined through communication between the clinicians and patients based on the suggestions and information provided by the SDM tool. This includes anticoagulation strategies that have a corresponding net clinical benefit (NCB), cost of each anticoagulant, blood examination of warfarin, and other relevant considerations. Clinicians will prescribe dosage regimens and order appropriate laboratory monitoring based on the recommendations of the SDM tool. Furthermore, this SDM tool can also assist clinicians with anticoagulation regimes in AF patients with specific circumstances, such as adjuvant bridging therapy, periprocedural anticoagulation recommendations, and drug regimen adjustments for end-organ function, weight, and concomitant interactions. With the help of the SDM tool, pharmacists can provide comprehensive patient education, including indications for the therapy, medication intake, medication interactions, laboratory monitoring, activity, diet, side effects, pregnancy, procedures, safety precautions, and self-care. The SDM tool will also enable the tracking of bleeding and other adverse events relevant to anticoagulation, as well as assessing patients’ knowledge, adherence, and satisfaction with anticoagulation therapy. The tool will automatically schedule the follow-up scheme, and the anticoagulation therapy will be reassessed based on the follow-up data of the patients. The records and information of the patients will be obtained from the SDM tool cloud platform. In contrast, the control group will receive the usual care based on the clinicians’ usual approach.

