#### Secondary outcomes

The study’s secondary outcomes include the accordance of stroke prophylaxis for AF according to the current guidelines, the percentage of time in the target INR range for patients using warfarin, the occurrences of major bleeding and thrombosis events, and the OAC knowledge, adherence, and satisfaction of AF patients receiving anticoagulation therapy. The study will evaluate stroke prophylaxis for AF using a flow chart (Fig. 2) and guidelines for dabigatran, rivaroxaban, and edoxaban (Table 2). The anticoagulation quality of warfarin will be assessed using the TTR, and the therapeutic range of INR for patients with AF is set between 1.8 and 3.0 [34]. The study considers TTR levels of 65% or higher as good anticoagulation quality. Thrombosis events, including ischemic stroke, systemic embolism, and transient ischemic attacks, will be confirmed by imaging methods such as ultrasound, CT, or MRI. To evaluate patients’ knowledge, adherence, and satisfaction with anticoagulation therapy, the study will use AKT, MARS-5, and ACTS. The AKT comprises 28 items assessing the general anticoagulation knowledge for all available OAC and a specific section for VKA therapy. The MARS-5 assesses common patterns of nonadherent behavior, and the ACTS evaluates the burdens and benefits of anticoagulation treatment and its overall impact (see Additional file 2).

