### Statistical analyses

In accordance with standard practice, continuous variables will be presented as means ± standard deviation, while categorical variables will be expressed as proportions. The Kolmogorov–Smirnov test will be utilized to determine the normality of the data. Student’s *t*-test or Mann–Whitney’s *U*-test will be applied to compare two groups, depending on the distribution of the data. For categorical data, comparisons between the groups will be performed using the chi-square or Fisher’s exact tests. Time in therapeutic range (TTR) will be evaluated for patients on warfarin. Multiple imputations will be used to fill in missing values, and both per-protocol (PP) analysis and intention-to-treat (ITT) analysis will be conducted. Subgroup analyses will be performed based on patients’ age groups, treating hospitals, liver or kidney function, the type of anticoagulants used, etc. Statistical significance will be assumed for *p* values less than 0.05. All statistical analyses will be conducted with the IBM SPSS version 22.0 software.

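### Two planned subgroups do not fit the design: treating hospital has one arm per centre, and type of anticoagulant is chosen after allocation on the tool's advice

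*Protocol article*

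**What the plan says.** The Statistical analyses section lists subgroup analyses by age group and by "treating hospitals, liver or kidney function, the type of anticoagulants used, etc". It compares the two groups with standard two-sample tests.

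On allocation, Study design states: "The clusters will be randomly assigned to either the SDM or control group". The abstract describes the trial as "involving 440 patients with AF in 8 community health service centers (clusters) in Shanghai, China". Randomization and blinding adds "The intervention provided to patients with AF will be grouped by clinicians in a single community health service center" and "The allocation results of each community health center will be told to the administrators by telephone". The introduction to the Interventions section says "Community health service centers that are randomized to the SDM group will utilize the SDM tool to manage AF patients".

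On drug choice, the same introduction says of SDM centres: "The anticoagulation regimens for AF patients will be determined through communication between the clinicians and patients based on the suggestions" that the tool provides. The section describing the tool adds that risks and net clinical benefit are recalculated during follow-up and that recommended regimens change accordingly.

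On restricted outcomes, Secondary outcomes limits TTR to warfarin users and refers to knowledge, adherence and "satisfaction of AF patients receiving anticoagulation therapy". The tool section describes the questionnaires (AKT, MARS-5, ACTS) in the same restricted way. The Follow-up section and Table 3, however, schedule them for both arms at every visit without that restriction.

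**The concern.** A subgroup analysis of a randomised trial asks whether the treatment effect differs between kinds of patient. It needs both arms in each subgroup, and a subgroup variable that the intervention cannot have changed.

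Treating hospital fails the first condition. The centre is the unit of randomisation, so any contrast between hospitals in different arms mixes the arm effect with every other difference between those centres.

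Type of anticoagulant used fails the second. Changing anticoagulant use is one of the trial's purposes, according to the abstract's discussion. If the tool moves certain patients from one drug to another, the warfarin users in the SDM arm are no longer the counterparts of the warfarin users in the control arm. A difference in bleeding between them could then reflect who was given the drug.

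TTR carries the same limitation, and so would the questionnaire outcomes if they are analysed only in patients on anticoagulation.

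**Working it through.** The plan attaches no figure to these subgroups. Its sample size (88 per arm, 110 after 20% loss, 440 in total with a design effect of 2) reproduces with 20% against 5% bleeding, 80% power, two-sided 5% and a continuity correction. The present point does not depend on it.

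**1. Treating hospital**

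Inputs: 8 centres, 440 patients, one allocation per centre. The average is 440 / 8 = 55 patients per centre, all in one arm.

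- Model with a separate level for each centre plus an arm effect: 8 centre indicators + 1 arm indicator = 9 columns. The arm indicator equals the sum of the indicators of the SDM centres, so the rank is 8. The arm effect cannot be separated from the centre levels.
- Model with centre-by-arm terms: 8 + 8 = 16 columns. For an SDM centre the product repeats the centre indicator; for a control centre it is zero throughout. The rank is again 8.

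The missing information is the other arm within each centre. More patients per centre would not supply it.

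**2. Type of anticoagulant used**

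The document gives no drug shares by arm, so the following is an illustration and every input is assumed. Half the patients are high risk. Bleeding is 30% in high-risk and 10% in low-risk patients, whatever the arm or drug, so there is no true effect. In the control arm 40% of each risk group take warfarin. In the SDM arm low-risk patients stay at 40%, while warfarin use in high-risk patients varies.

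Bleeding in a drug group = (0.5 × share of high-risk on the drug × 0.30 + 0.5 × share of low-risk on the drug × 0.10) / (0.5 × share of high-risk + 0.5 × share of low-risk).

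Control arm, warfarin: (0.5 × 0.4 × 0.30 + 0.5 × 0.4 × 0.10) / 0.4 = 20%. Other drug: also 20%.

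SDM arm with 20% of high-risk patients on warfarin: (0.03 + 0.02) / 0.30 = 16.7%. Other drug: (0.12 + 0.03) / 0.70 = 21.4%.

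| High-risk SDM patients on warfarin | False difference, warfarin | False difference, other drug |
|---|---|---|
| 40% (tool changes nothing) | 0 | 0 |
| 30% | −1.4 points | +0.8 points |
| 20% | −3.3 points | +1.4 points |
| 10% | −6.0 points | +2.0 points |

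The all-patient comparison stays at zero in every row. In the 20% row, for example, 0.30 × 16.7% + 0.70 × 21.4% = 20%, as in the control arm.

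**3. Restricted outcomes**

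| Source in the protocol article | Who is covered |
|---|---|
| Secondary outcomes, TTR | Warfarin users |
| Secondary outcomes and tool section, questionnaires | Patients receiving anticoagulation |
| Follow-up section, questionnaires | Both arms at each follow-up, no drug condition |
| Table 3, questionnaires | D0 and every visit, no drug condition |

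TTR cannot be defined outside warfarin users. For the questionnaires, the document does not settle the analysis population.

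**The case against.** Several counter-arguments carry weight.

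- *Treating hospital is undefined.* The only treating sites named are the eight centres. Grouping centres by a type that includes both arms could be estimated, though with very few clusters, but the document does not say this is meant. Nor does the phrase placing randomisation after AF confirmation change matters, because the surrounding text allocates whole centres. It does stand that descriptive results by centre remain possible.
- *The list is indicative and detail may sit in the analysis plan.* This is fair for the form of the interaction tests and the full subgroup list. It does not cover the two named variables, which conflict with the design as stated.
- *TTR is openly limited to warfarin users and is secondary.* This stands. It is not a design error and needs only a label.
- *Guideline accordance is already a secondary outcome.* It captures part of what the tool does to prescribing, with no stated restriction to treated patients. It does not make drug type a valid subgroup.

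A reader might infer that the SDM arm will look worse on adherence or TTR because it brings reluctant patients onto treatment. That is one possible scenario; the document supports neither that direction nor any size. A reader might also use the 29.5% anticoagulation rate in the Background to work out how few patients the restricted comparisons would contain. That figure comes from a cross-sectional survey and not from usual care in these centres. The SDM-arm rate is unknown, and such counts would not measure bias. Finally, a reader might take the questionnaires as definitely restricted to treated patients; Follow-up and Table 3 point the other way.

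**Conclusion.** The point holds for the two named subgroup variables. For treating hospital it is exact: 0 of 8 centres contain both arms, so a treatment effect by centre is not estimable. This rests only on whole-centre allocation, which the article states in several places. For type of anticoagulant it is a matter of principle: the comparison is not protected by randomisation, its bias could go either way, and it is zero if the tool does not alter drug choice. The percentage-point figures above show only that a false difference can arise; they do not estimate it.

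TTR and the questionnaires are secondary notes, one of labelling and one of inconsistent populations. Age is sound as a subgroup. Liver and kidney function are sound if the D0 value is used; Table 3 measures both at every visit and the analysis section does not say which value counts. The primary all-patient bleeding comparison is untouched, so the change is worth making but does not bear on the trial's main result.

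**What to change.** 1. Delete treating hospital as a treatment-effect subgroup. Show results by centre descriptively.
2. Replace type of anticoagulant used with variables fixed at D0: age, CrCl, Child–Pugh, CHA2DS2-VASc and HAS-BLED. State that liver and kidney function subgroups use D0 values. Anticoagulant use at entry is a poor substitute, since Settings and participants describes newly diagnosed patients and the subgroup could be nearly empty.
3. Report the drug received, including none, as an outcome by arm in all enrolled patients.
4. Keep TTR, but label its between-arm comparison as non-randomised because it is limited to warfarin users.
5. Reconcile Secondary outcomes and the tool section with Follow-up and Table 3 on who completes the questionnaires and who is analysed. Analyse AKT in all enrolled patients; its section specific to VKA therapy shares the limitation of TTR. Label any comparison limited to patients on anticoagulants as non-randomised.

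The cost is revised wording and a few extra tabulations. As scheduled in Table 3, the questionnaire and D0 data are already due to be collected, and drug usage is among the items to be recorded.

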### Outcomes

The outcomes will be collected at each follow-up time point (1st, 3rd, 6th, 12th, 18th, and 24th months).

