#### Primary outcomes

While thrombotic events are a critical consequence of AF, the incidence rate of these events in patients who are adequately anticoagulated is generally lower than the incidence of bleeding events. Consequently, the study’s primary outcomes comprise any bleeding events, both major and minor. Major bleeding events [32] include fatal hemorrhage, life-threatening bleeding, and severe bleeding requiring treatment or assessment. Severe bleeding can manifest as gastric intestinal hemorrhage, joint hematoma, retroperitoneal hemorrhage, fundus hemorrhage, urine, hemoptysis, or require blood transfusion of at least two units. In contrast, minor bleeding events, such as mild nasal hemorrhage, endoscopic hematuria, skin stasis, or mild hemorrhoids, do not lead to serious consequences [33].

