### Sample size

This multicenter, cluster-randomized clinical trial aims to evaluate the occurrence of bleeding events as the primary outcome. The anticoagulation bleeding rate of patients with AF in our hospital was previously found to be 20% [24], and an effective intervention reduces the incidence of bleeding by 15% [35]. We set the power at 80% with a bilateral two-tailed significance of 5%. To achieve a sample size of 88 cases in both the intervention and control groups, with a 20% loss to follow-up rate, we estimated a minimum of 110 cases in each group. However, taking the clustering into account, we increased the sample size to account for the design effect to achieve the required statistical power under cluster randomization. Therefore, using the bleeding rate as the calculating target and a design effect of 2, we estimated a sample size of 440, which was calculated using the PASS software version 15.

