## Discussion

A prospective, cluster-randomized trial will be conducted to evaluate the effectiveness of a novel SDM tool in reducing bleeding events and improving guideline compliance for stroke prophylaxis in AF patients. Additionally, the trial aims to evaluate the impact of the SDM tool on anticoagulation quality, patient adherence, and satisfaction.

In the current healthcare landscape, pharmacists have become a vital link in the chain of patient care, as they are able to provide patients with critical support when it comes to managing their chronic illnesses and medications, especially when it comes to anticoagulation decisions [36, 37]. Studies have shown that when pharmacists are involved in shared decision-making, patients benefit from better medication appropriateness and adherence [38, 39]. To further explore the potential benefits of pharmacist involvement, our research will incorporate pharmacists as part of the patient care team in a combined pharmacy clinic. Specifically, we will investigate the role of pharmacists in ensuring that anticoagulant prescriptions for the AF management are appropriate and in line with guidelines.

Although clinicians show a wealth of interest and willingness in participating in research, their heavy clinical workload hurdles the progress of clinical studies, especially when they need to manually enter basic patient data into management tools. It will be very convenient and useful to seamlessly integrate data from hospital information systems (HIS) into mobile healthcare tools [40]. By integrating data, mobile healthcare tools can directly capture patient characteristics without relying on the manual input of healthcare workers. Such integration enhances the accuracy and efficiency of health management [40, 41]. Nevertheless, there are no established standards for integrating HIS and mobile healthcare tool data in this study. In addition, ensuring the online safety of patient information is a significant concern, making the process of seamless data integration complex [42]. This process necessitates permissions from various departments such as the Department of Information, the Department of Medicine, and the Ethics Committee. Therefore, more efforts should be made to establish data exchange standards between HIS and mobile healthcare tools, which will accelerate the development of mobile healthcare applications [41].

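### A single p < 0.05 rule covers the primary outcome, seven secondary outcomes and an open-ended list of subgroups, so chance findings outside the primary comparison would be declared significant more often than 5% suggests

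*Protocol article*

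**What the plan says.** The Statistical analyses section names two-group comparisons only: t or Mann–Whitney tests for continuous data, and chi-square or Fisher tests for categorical data. It then says: "Subgroup analyses will be performed based on patients’ age groups, treating hospitals, liver or kidney function, the type of anticoagulants used, etc". The decision rule follows directly: "Statistical significance will be assumed for *p* values less than 0.05". No result is exempted from it.

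The outcomes it covers are these:

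- **Primary.** One composite: "the study’s primary outcomes comprise any bleeding events, both major and minor". The Sample size section powers the trial on bleeding alone: "We set the power at 80% with a bilateral two-tailed significance of 5"%.
- **Secondary.** The list begins with "the accordance of stroke prophylaxis for AF according to the current guidelines, the percentage of time in the target INR range for patients using warfarin" and continues with "the occurrences of major bleeding and thrombosis events, and the OAC knowledge, adherence, and satisfaction of AF patients receiving anticoagulation therapy". That makes seven: guideline accordance, TTR, major bleeding, thrombosis, knowledge (AKT), adherence (MARS-5) and satisfaction (ACTS).

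The Background calls only communication and cost-effectiveness exploratory. The Randomization and blinding section says that data analysts are not blinded.

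**The concern.** The article sets a rule for declaring significance and makes no distinction between the one powered comparison and everything else. That matters because conclusions are planned from the secondary family. The Background states the trial's aim as better quality of anticoagulation, adherence and satisfaction, all measured by secondary outcomes. The Discussion says that the trial will "evaluate the effectiveness of a novel SDM tool in reducing bleeding events and improving guideline compliance for stroke prophylaxis in AF patients", which puts a secondary outcome beside the primary one.

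The subgroup clause is the weakest part. The list has no end, no method for comparing effects between subgroups is named, and factors can be added by analysts who know the allocation. With only two-group tests named, the natural way to follow the text is to compare the arms within each subgroup and call any p < 0.05 significant. A benefit in one subgroup, or on one secondary outcome, could then be reported as significant when it is chance.

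**Working it through.** **The plan's own figure.** The article states no family-wise error rate. Its only related figure is the sample size for the primary outcome. Two proportions of 20% and 5%, two-sided 5%, 80% power, with continuity correction, give 88 per group. Then 88 / (1 − 0.20) = 110 per group, and 110 × 2 groups × design effect 2 = 440. This reproduces the plan. It confirms that the 5% level belongs to one bleeding comparison, so the secondary and subgroup tests do not change the primary error rate or the 440.

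**Assumptions for the rest.** The tool has no effect on any outcome. Each single test holds its nominal level: 5% two-sided, hence 2.5% in the direction of benefit. Correlations between outcomes are not in the article, so a range is shown.

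**Seven secondary outcomes, each tested once**

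- Independent, any p < 0.05: 1 − 0.95^7 = 0.302.
- Independent, false benefit: 1 − 0.975^7 = 0.162.
- Correlated: simulation of seven equally correlated normal statistics, counting |Z| > 1.96 (any) or Z > 1.96 (benefit).

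| Correlation | Any p < 0.05 | False benefit |
|---|---|---|
| 0 | 30% | 16% |
| 0.5 | 23% | 12% |
| 0.8 | 15% | 7% |

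**Subgroups on the primary outcome.** The article gives neither the number of factors nor their levels, so this is an illustration: three independent, balanced two-level factors, with the arms compared within each level, giving six tests.

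- If all six were independent: 1 − 0.95^6 = 0.265 for any and 1 − 0.975^6 = 0.141 for benefit.
- They are not independent, because the same 440 patients are cut three ways. Simulating null trials of 440 patients (20% bleeding in both arms) gives 0.21 for any and 0.11 for benefit.

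**Treating hospitals as a subgroup.** The trial randomises eight community health service centers. If the treating hospitals are these centers, every patient at a center is in the same arm. There is then no between-arm comparison within a hospital, and no arm-by-hospital interaction can be estimated.

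**The case against.** The strongest reply has four parts.

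1. **The outcomes are already ranked.** There is one powered primary outcome, and the rest are headed secondary. This stands: the confirmatory test keeps its 5%, and a reader who infers that the plan has no hierarchy at all goes too far. What is absent is any difference in how the two tiers are declared significant.

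2. **Multiplicity detail belongs in the SAP, which is not shown, and unadjusted supportive secondary outcomes are common.** This stands for a testing order, a Holm correction or the choice of a deciding visit, and none of these is asked for here. It does not cover what the article itself states: a significance rule without exemption and a subgroup list without end.

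3. **Testing at six visits is not planned.** A reader might take "The outcomes will be collected at each follow-up time point (1st, 3rd, 6th, 12th, 18th, and 24th months") to mean 7 × 6 = 42 tests, for which independence would give 1 − 0.95^42 = 88% for any false positive. The sentence describes data collection. Nothing says that the arms are tested at each visit, and bleeding, thrombosis and TTR accrue over follow-up. That count is therefore not used.

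4. **The subgroup figure is constructed.** This is true. The article does not say that effects will be judged within levels, and liver and kidney subgroups may be unbalanced because severe impairment is excluded. The 21% shows the size of the problem under one plausible reading and is not a property of the plan.

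**Conclusion.** The point holds in a limited form. Followed as written, the rule would declare chance secondary or subgroup results significant several times as often as the 5% level of a single test suggests. The chance is about 15–30% for at least one of seven secondary outcomes and about 21% for six within-subgroup tests on bleeding.

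A reader might infer that a false claim of benefit is likely. The figures do not support that. In the beneficial direction they are about 7–16% and about 11%, against 2.5% for one test, and well short of even odds. Exceeding one half would need every visit tested with weak correlation, or many more tests, neither of which the article states.

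The result rests on true null effects, the assumed correlations, the illustrative subgroup structure, and each test holding 5%. The last assumption depends on clustering being handled in the analysis, which is a separate matter. The primary comparison and the sample size are unaffected.

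**What to change.** In the Statistical analyses section:

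- Confine the declaration of significance at two-sided p < 0.05 to the primary bleeding comparison.
- Report the secondary outcomes as estimates with 95% confidence intervals, labelled supportive.
- Close the subgroup list by deleting the final *etc.*, and label all subgroup analyses exploratory.
- Judge subgroups by an arm-by-subgroup interaction estimate with its confidence interval, not by p values within subgroups.
- State whether the treating hospitals are the randomised centers. If they are, drop that factor or keep it descriptive.

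This takes a few sentences and needs no extra patients or data. The small downside is that fewer secondary and subgroup results can be called significant.
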